### Moderator

#### T0, T1, T2, T3, T4, and 1-year follow-up measures (girls)

##### Self-reported self-control

Self-reported self-control will be assessed using the Dutch version of the 5-item Self-Control Measure (SCM; [86, 87]). Items will be rated on a 5-point Likert scale (“*not true at all*” = 1 to “*completely true*” = 5). Example items are “I have trouble saying no” and “I do certain things that are bad for me, if they are fun.” A higher sum score will reflect higher self-control (Cronbach’s *α* = 0.62 [88]).

### Mediators

#### T0, T1, T2, T3, T4, and 1-year follow-up measures (girls)

##### Self-reported trait mindfulness

Self-reported trait mindfulness will be measured with the Dutch adolescent version of the Comprehensive Inventory of Mindfulness Experiences (CHIME-A; [89, 90]). The CHIME-A assesses eight different aspects of mindfulness: awareness of internal experiences, awareness of external experiences, acting with awareness, accepting and nonjudgmental attitude, non-reactive decentering, openness to experiences, awareness of thought’s relativity, and insightful understanding. Its 24 items are scored on a 6-point Likert scale with higher scores indicating greater mindfulness skills. The subscales of the Dutch version of the CHIME-A have acceptable psychometric properties with Cronbach’s alphas ranging from 0.67 to 0.77 [90].

##### Self-reported emotion regulation

Self-reported emotional regulation will be measured with the Dutch version of the Difficulties in Emotion Regulation Scale (DERS; [91, 92]). The DERS is a 36-item self-report questionnaire developed to assess individuals’ identification, understanding, and modulation of their own emotions (Gratz & Roemer, 2004). Items are scored on six scales, labeled Lack of Emotional Awareness (6 items), Lack of Emotional Clarity (5 items), Difficulties Controlling Impulsive Behaviors When Distressed (6 items), Difficulties Engaging in Goal-Directed Behavior When Distressed (5 items), Nonacceptance of Negative Emotional Responses (6 items), and Limited Access to Effective ER Strategies (8 items). Items are scored on a 5-point scale ranging from 1 (*almost never*) to 5 (*almost always*). Subscale scores will be obtained by summing up the corresponding items. The subscales of the Dutch version of the DERS have satisfactory to high psychometric properties with Cronbach’s alphas ranging from 0.72 to 0.87. [92].

### Implementation measures

#### T1, T2, T3, T4

In order to study how implementation impacts the hypothesized effects of the HFPM program, the following variables will be studied:*Program dosage*, i.e., how much of the program has been followed, will be measured by the total amount of complete delivered training sessions within each dyad (one question) and the percentage of dyadic attendance to the sessions (one question). Data on both variables will be collected by the trainers, who will have to fill out a digital form after each training session.*Participant responsiveness*, i.e., the degree to which the program engages and stimulates the interest of the participants, will be measured by seven questions assessing rates of usefulness, perceived benefits, engagement, enjoyment, helpfulness, intentions to apply to daily life, and perceived success in applying to daily life. Girls will be asked to rate their answers on a 5-point Likert scale, ranging from “*not at all*” to “*very much*.” Data will be collected by digital questionnaires immediately following each training session.*The extent of participants’ self-reported practice outside of the training sessions* will be measured by the percentages of (1) completed activities (i.e., back-end data collected by the app), (2) completed daily state mood monitoring activities (i.e., back-end data collected by the app), and (3) completed daily mindfulness-based questions (i.e., back-end data collected by the app). Moreover, data on self-reported practice outside of the training sessions will be collected by asking girls to fill out digital questionnaires after each training session about the amount of self-reported mindfulness practices within their dyadic conversations, ranging from low [*once a week or less*], medium [*three times a week or less*], and high [*at least three times a week*].*Program fidelity*, i.e., the extent to which the delivered program corresponds to the original program will be collected using self-administered digital forms completed by the trainers after each lesson, reporting whether the scheduled activities were delivered (yes or no) and whether the trainers (yes or no) altered any activities. The fidelity forms will list all activities planned for each training session, based on the training manual. The PI will instruct the trainers on how to complete the form. Each item will have data on the percentage of activity completeness (i.e., the numerator will be the number of activities delivered, and the denominator will be the total number of activities planned), and percentage of alterations (i.e., the numerator will be the activities instructors reported changing, and the denominator will be the number of activities planned). A fidelity variable for each dyad will be calculated as follows: fidelity = % completeness × (1 − % alteration). Dyads will then be divided into two groups according to the level of fidelity: those that received ≥ 80% of the proposed activities will be considered to have completed the program, whereas those that received < 80% of the activities will be considered to have incomplete implementation.*Program quality*, i.e., how well the different program components are delivered, will be observed via the recorded Teams-training sessions (protected Teams-environment of Rotterdam University of Applied Sciences) with a standardized measure, the Dutch version of the Mindfulness Based Interventions – Teacher Assessment Criteria; MBI:TAC; [64, 93]). The six teaching competence domains within the MBI:TAC are (1) coverage, pacing, and organization of the session curriculum; (2) specific interpersonal relational skills; (3) skillful guiding of formal mindfulness meditation practices; (4) specific methodologies for conveying the course themes through interactive inquiry, (5) group dialog and didactic teaching; and (6) effective holding of the group teaching/learning environment. This instrument will also be used in the training program including supervision during which the criteria are used as a developmental tool to offer clear feedback to the trainers and to identify foci for development.*Treatment contamination*, i.e., monitoring of the control group, will be measured by an online questionnaire for parents at T0, T2, and T4 with one question: “Did your child attend a mindfulness-based course in the last two or three months, and if yes, please mention the name of the course”.

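### The two-group fidelity split is announced on the fidelity score but cut on the share of activities received, so one dyad can fall in either group; the practice categories also overlap at three times a week

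*Protocol article*

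**What the plan says.** All the text is in the Protocol article, Implementation measures (T1, T2, T3, T4).

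- Program fidelity is described as "the extent to which the delivered program corresponds to the original program".
- Completeness: "the numerator will be the number of activities delivered, and the denominator will be the total number of activities planned".
- Alteration: "the numerator will be the activities instructors reported changing, and the denominator will be the number of activities planned".
- The fidelity variable for each dyad is completeness multiplied by one minus alteration.
- The grouping: "Dyads will then be divided into two groups according to the level of fidelity". After the colon the rule reads "those that received ≥ 80% of the proposed activities will be considered to have completed the program". Dyads below 80% of activities are called incompletely implemented.

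A separate item in the same section asks girls, after each session, how often they practised mindfulness within their conversations. Low is up to once a week, medium is "three times a week or less", and high starts at three times a week.

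The section's stated purpose is to study how implementation bears on the hypothesised programme effects.

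**The concern.** The lead-in sentence and the cut name different variables. The lead-in refers to the score computed just before it, which falls when trainers change activities. The cut refers to activities received, which is the section's own definition of completeness and does not change however many activities were altered. A dyad with at least 80% delivered and a score below 80% is therefore complete under one sentence and incomplete under the other. No other part of the article says which applies.

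If the rule is left open, an analyst must choose it later, possibly with results in view, and the choice decides which intervention dyads count as having completed the programme.

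Two smaller defects sit beside this. The score multiplies two proportions that share the denominator of planned activities, so it is not the share of the programme delivered as designed. The practice categories overlap, and if only the category is stored, the overlap cannot be undone afterwards.

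**Working it through.** **Inputs.** From the section: P activities planned, D delivered, X altered. Completeness C = D/P, alteration A = X/P, score F = C × (1 − A). The article gives no value for P and no expected alteration rate, so the values below are illustrations. I assume altered activities are among those delivered (X ≤ D); the section does not state this.

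**Step 1: the two rules.** Received rule: complete if C ≥ 80%. Score rule: complete if F ≥ 80%. U = (D − X)/P = C − A is the share of planned activities delivered unaltered.

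| C | A | F = C(1 − A) | U = C − A | Received rule | Score rule |
|---|---|---|---|---|---|
| 100% | 20% | 80.0% | 80% | complete | complete |
| 100% | 30% | 70.0% | 70% | complete | incomplete |
| 90% | 11% | 80.1% | 79% | complete | complete |
| 90% | 15% | 76.5% | 75% | complete | incomplete |
| 85% | 6% | 79.9% | 79% | complete | incomplete |
| 80% | 1% | 79.2% | 79% | complete | incomplete |
| 50% | 50% | 25.0% | 0% | incomplete | incomplete |

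The score rule tolerates alteration up to 1 − 0.80/C: 20% at C = 100%, 11.1% at 90%, 5.9% at 85% and 0% at 80%. The received rule sets no limit. Since F ≤ C always, disagreement is possible only as complete by receipt and incomplete by score, never the reverse.

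**Step 2: how much comes from the denominator.** F − U = C − CA − C + A = A(1 − C), which is zero only if nothing was altered or everything was delivered. On the line F = 0.80, A = 1 − 0.80/C, so the gap is (1 − 0.80/C)(1 − C) = 1.8 − C − 0.80/C. It is largest at C = √0.80 = 89.4%, where it equals 1.8 − 2 × 0.8944 = 0.011, or about 1.1 points. Far from the line it is larger: 25 points in the last row of the table.

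**Step 3: relative weight.** I counted every possible pair (D, X) with X ≤ D. For P = 100 there are 5151 pairs; the two rules disagree on 1674, while replacing F by U in the score rule changes 6. For P = 70 there are 2556 pairs; the rules disagree on 840 and the denominator changes none. These are counts of possibilities under assumed P, not expected frequencies.

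**Step 4: effect of counting alteration over delivered activities.** C × (1 − X/D) = (D/P) × (D − X)/D = (D − X)/P = U exactly. For 90 delivered and 15 altered of 100: 0.90 × (1 − 15/90) = 75%.

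**Step 5: practice categories.** Three times a week meets both the medium and the high definition. Zero or one meets low and, as worded, medium too.

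**The case against.** The strongest reply is that the colon introduces levels of the variable just computed. On that reading the cut means a score of at least 80%, and the only fault is a loosely chosen verb; otherwise the score would be computed for no stated purpose. This is plausible, and it is the reading the fix adopts. It does not remove the problem, because the written cut speaks of activities received and of completing the programme, which is the language of completeness.

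A reader might infer that the shared denominator is what puts a dyad in both groups. It is not: in the 90%/15% example both figures, 76.5% and 75%, lie below 80%. Nor does the article say that the score is the share delivered unaltered; that meaning is inferred from its definition of fidelity. The denominator point therefore stands only as a remark on what the continuous score measures.

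On practice, the categories run in order from low to high, so most readers would take medium as what lies above low. That softens the lower overlap but leaves exactly three times a week unresolved.

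On consequence, the article names the fidelity grouping in none of its analyses for hypotheses 1 to 9. It reports only principal features and refers to an analysis plan that is not shown. This stands and limits the point, but the article itself fixes the formula, cut and categories, so their conflict is not detail left to that plan.

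**Conclusion.** The point holds as a contradiction in a stated rule. Any dyad with at least 80% delivered and a score under 80% changes group with the sentence followed. At full delivery that needs alteration above 20%; at exactly 80% delivery any alteration suffices. How many dyads this would affect cannot be said, because the documents give neither the number of planned activities nor an expected alteration rate.

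The denominator issue is minor at the cut (at most about 1.1 points, given X ≤ D) and matters mainly if the score is used as a continuous variable. The overlap at three times a week is real and separate from the fidelity split.

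A reader might infer that the trial's effect estimates are at risk. The documents do not support that: fidelity is recorded by trainers and so exists only for the intervention arm's planned 80 dyads, and neither the randomised comparison, the primary outcomes nor the sample size uses it. This is a desirable clarification, not a threat to the main results.

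**What to change.** 1. State that the 80% line applies to the fidelity score, and replace the wording about activities received accordingly.
2. Count alteration over delivered activities, so that the score equals the share of planned activities delivered unaltered. State that only delivered activities can be marked as altered, how a replaced activity is logged, and that a dyad with nothing delivered scores zero. Completeness minus alteration over the planned denominator is a weaker alternative: if replaced activities are logged as altered but not delivered, it can go negative (40% delivered and 60% replaced gives −20%).
3. Make the practice categories mutually exclusive, or record the number of times per week and form categories from it.

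Items 1 and 2 are wording changes, since the trainer forms already list every planned activity with delivery and alteration. Item 3 changes what is collected and can apply only to sessions not yet held. Under the Timeline section, T1 starts in February 2024 for cohort 1 and December 2024 for cohort 2, so a late change would leave the cohorts with different items. The analysis should then say how earlier answers are mapped.

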### Sample screening and cRCT

We will include 160 high-risk friendship dyads who are primarily characterized by high levels of co-rumination within their daily interaction patterns. “High risk” is defined on the dyadic level and implies that at least one of the two girls of one friendship dyad, or both girls, should have a score of at least one standard deviation above the mean co-rumination screening score (see below). Therefore, approximately 1000 girls of approximately 100 8th and 9th classes of Koers VO schools with written informed consent will be screened on maladaptive co-rumination through the Co-rumination Questionnaire-Short [21]. All girls will receive an email with a secured link to the online questionnaire and a request to complete the questionnaire within 1 week. A first reminder will be sent after 1 week, a second reminder after 2 weeks and finally, the research team will contact the girls by phone with a final prompt to complete the questionnaire.

After completing the screening procedure, all dyads with at least one of the two girls with a score of at least one standard deviation above the overall mean co-rumination screening score will be eligible for inclusion in the cRCT. Finally, 160 Dutch girls from age 13 to 15 years old with high levels of maladaptive co-rumination and their good or best friend from age 13 to 15 years old within the same secondary school (*n* = 320 girls; 160 dyads) will be included in the cRCT. In anticipation of 20% dropout, 16 dyads will be placed on a waiting list.

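### The fidelity rule cuts a continuous score into two groups at 80% and does not say whether its denominator covers all 14 sessions or only the lessons with a form

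*Protocol article*

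**What the plan says.** All of this is in the protocol article, Implementation measures (T1, T2, T3, T4), under the program fidelity item unless stated otherwise.

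- **Source.** The data come from "self-administered digital forms completed by the trainers after each lesson". Trainers report whether each scheduled activity was delivered and whether any was altered.
- **Content of the forms.** "The fidelity forms will list all activities planned for each training session, based on the training manual".
- **Completeness.** The numerator is the number of activities delivered, and "the denominator will be the total number of activities planned".
- **Score per dyad.** "fidelity = % completeness × (1 − % alteration").
- **Split.** "Dyads will then be divided into two groups according to the level of fidelity", and "those that received ≥ 80% of the proposed activities will be considered to have completed the program". Dyads below 80% are labelled as incomplete implementation.
- **Dosage, a separate item.** Trainers report the number of complete sessions delivered within each dyad and "the percentage of dyadic attendance to the sessions (one question"). Neither is dichotomised, and neither enters the fidelity rule.

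The section on the HFPM app-based mindfulness training program sets the number of manualised weekly sessions at 14. The implementation variables are there to study how implementation affects the hypothesised effects.

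**The concern.** Three features of the rule work against that purpose.

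1. A graded score is calculated and then replaced by a yes/no grouping. A dyad at 79% is separated from one at 81% and pooled with one at 20%.
2. The label refers to what dyads received, while the input is what trainers say they delivered. Whether each girl was present plays no part in it.
3. No rule covers a lesson that never takes place. The forms are filled in after lessons, so an unheld lesson may produce no form. Whether its activities still count in the denominator decides how a dyad that stops early is graded.

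At stake is whether the completion status can be reproduced from the text, and how well the implementation analyses can detect a relation between fidelity and outcome.

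**Working it through.** The 80% cut-off is a definition, so there is no derived figure to reproduce. The checks below apply the rule as written.

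**1. The two denominators.** Inputs: 14 sessions and the 80% cut-off, both from the protocol article. Assumptions: an equal number of activities per session and no alterations, so that fidelity equals completeness. Let *s* be the sessions held and *c* the share of activities delivered in them.

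- Forms only: completeness = *c*.
- Whole program: completeness = *s* × *c* / 14.

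| Sessions held | *c* | Forms only | Whole program |
|---|---|---|---|
| 5 | 1.0 | 100%, completed | 5/14 = 35.7%, incomplete |
| 7 | 1.0 | 100%, completed | 7/14 = 50.0%, incomplete |
| 11 | 1.0 | 100%, completed | 11/14 = 78.6%, incomplete |
| 12 | 1.0 | 100%, completed | 12/14 = 85.7%, completed |
| 12 | 0.9 | 90%, completed | 10.8/14 = 77.1%, incomplete |

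The same dyad can fall in opposite groups. Under the whole-program reading, no dyad with 11 or fewer sessions can qualify.

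**2. Information kept by the split.** For a normal score cut so that a fraction *p* lies on one side, the share of linear information kept is φ(z_p)² / [p(1 − p)].

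- p = 0.50: z = 0, φ = 0.3989; 0.1592/0.25 = 0.637, so about 36% is lost.
- p = 0.79: 0.501 is kept, so about half is lost.
- p = 0.80: z = 0.842, φ = 0.2800; 0.0784/0.16 = 0.490, so about 51% is lost.

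The article gives no expected share of dyads above the cut-off, so these are points on a range and not a forecast.

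**3. Received against delivered.** The numerator counts activities delivered; the classification sentence speaks of activities received. Attendance, the item that could link the two, sits under dosage as a percentage for the dyad and does not enter the rule.

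**4. A related loose end.** Dyads are grouped by level of fidelity, which is the product of completeness and (1 − alteration), but the cut-off is worded as activities received, which is completeness alone. With 100% completeness and 25% alteration the product is 1.00 × 0.75 = 75%. With 90% and 15% it is 0.90 × 0.85 = 76.5%. Both dyads pass on completeness and fail on the product.

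**The case against.** The case for leaving the text alone has real force.

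- **Dose is kept elsewhere.** A reader might infer that the split discards most of the information on dose. The documents do not support that. Sessions delivered, dyadic attendance, app back-end percentages and self-reported practice are all retained without a cut-off. A dyad that stops after session 5 is still recorded as having had five sessions. Only the fidelity score is coarsened, and by more than half only if about 79% or more of dyads fall on one side.
- **The whole-program denominator is the more natural reading.** The text refers to the total number of activities planned, the training manual and completing the program. A reader might infer that early leavers *will* be counted as completers. The documents support only that they could be, under the other reading.
- **No count of misgraded dyads follows.** A reader might take the dropout figure ("In anticipation of 20% dropout, 16 dyads will be placed on a waiting list") and work out how many dyads are wrongly graded and how far an effect is diluted. That would equate study dropout with stopping the program, ignore replacement up to the end of Phase 1, and need assumed effects that the article does not give.
- **No completer comparison is specified.** The article does not contrast completers with non-completers, so criticism of such a contrast has no target in the text. How implementation variables enter a model may be set out in the SAP.
- **Delivered and received largely coincide for a dyad.** Each dyad has its own trainer and the two girls take part together. Girls also answer questionnaires after each session, and 10% of videotapes are rated for fidelity.

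All of this narrows the point without removing it. The rule is stated in the article, it does split a score already in hand, it has no provision for unheld sessions, and it does not use attendance.

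**Conclusion.** The point holds in limited form. The split at 80% loses about 36% of the linear information in the fidelity score at equal groups and about 51% at 80/20. These figures assume a roughly normal score; the actual score has a ceiling of 100% and may be skewed. The denominator is not fixed for sessions that are not held: a dyad with 5 of 14 sessions scores 100% on one reading and at most 35.7% on the other, given equal activities per session. Completion status therefore cannot be reproduced from the text alone, and it describes receipt without using attendance.

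The consequence is confined to the implementation analyses. None of the hypothesis tests under Statistical methods for primary and secondary outcomes uses the split, so the primary and secondary results are not touched. The change is worth making because it costs almost nothing.

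**What to change.** In the program fidelity item of Implementation measures:

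1. State that the denominator is all activities of the 14 manualised sessions, and that the activities of a session not held count as zero. In the same sentence, say whether the 80% applies to completeness or to the product with alteration.
2. Use the continuous score, which is already computed for each dyad, as the implementation variable. Keep the 80% split for description only.
3. Record attendance for each girl on the existing trainer form, so that what was received can be scored and not only what was delivered.

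The cost is one more tick on a form that trainers already complete and a few words in the text. The completion rate is likely to look less favourable, because dyads with 11 or fewer sessions can no longer count as having completed the program.
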